# Investigating the feasibility and effectiveness of a modular treatment program for children and adolescents with depression and interpersonal problems: study protocol of a quasi-experimental pilot feasibility trial (CBASP@YoungAge)

**DOI:** 10.1186/s40814-022-01091-3

**Published:** 2022-07-11

**Keywords:** Depression, Psychotherapy, Children, Adolescents, Caregiver involvement, Modular treatment, CBASP

## Abstract

**Background:**

Depression is a serious disorder in childhood and adolescence. Affected children and adolescents show significant impairments in various aspects of life. Studies on the effectiveness or efficacy of psychotherapy in depressed children and adolescents are qualitatively very heterogeneous and reveal small effect sizes. There is thus a need to better tailor psychotherapy approaches to these age groups to improve outcomes like parent-child relationship, symptomatology, or quality of life.

To address this gap, we designed a modular, individualized treatment program for children and adolescents based on the Cognitive Behavioral Analysis System of Psychotherapy (CBASP) including caregiver involvement.

**Method:**

This quasi-experimental pilot feasibility trial is a phase 1 to phase 2 study investigating the feasibility and effectiveness of CBASP@YoungAge by including an intervention group (CBASP@YoungAge) and a treatment-as-usual control group. The treatment of depressive symptoms as well as interpersonal problems with primary caregivers are the main targets of CBASP@YoungAge. Personalization is ensured concerning the treatment course, caregivers’ involvement, and the patient’s age. The primary outcome relates to two areas: the feasibility of the CBASP@YoungAge treatment program in an outpatient context and a change in patients' depressive symptomatology from before to after treatment. We conduct a brief process evaluation after each session in the intervention group to closely monitor the treatment process and examine feasibility from the therapists' and patients' perspectives and mechanisms of symptom change. In addition, we consider interpersonal behavior between children and caregivers, parenting behavior, and monitor the global-health-index in children and parents as secondary outcomes. Pre-, post-, and follow-up data are evaluated.

**Discussion:**

This is the first study of a modular-based intervention program for children and adolescents with depression and a clear focus on the interpersonal problems between the depressed young patient and her/his caregiver. It will provide important knowledge on the feasibility and effectiveness of the program and potential benefits of including caregivers in psychotherapy. Based on this study’s results, we plan a multicenter, randomized, controlled trial whose long-term aim is to improve the psychotherapeutic care of young patients with depression while preventing persistent courses of depressive disorders.

**Trial registration:**

German Clinical Trials Register, DRKS (identifier DRKS00023281). Registered 17 November 2020–Retrospectively registered

**Supplementary Information:**

The online version contains supplementary material available at 10.1186/s40814-022-01091-3.

## Background

Depression in childhood and adolescence is widespread and debilitating at every stage of development [1–4]. Children and adolescents suffer from the same main depressive symptoms as adults, however, children and adolescents often perform worse at school, have social network difficulties, and somatoform symptoms [5, 6]. When depressive symptoms are not alleviated, the disorder tends to persist in adulthood [7, 8]. Early onset depression is associated with lower quality of life in childhood and adulthood, higher levels of comorbidities, and with other medical and mental disorders [9] as well as more suicide attempts [10–14]. Persistent negative family and social consequences in childhood or adolescence are also common [6].

These findings suggest that there is a strong need for effective treatment of depression in these age groups through early and evidence-based interventions [7, 15]. There is growing research on the psychotherapy of depression in children and adolescents, but recent studies have delivered heterogeneous results and only low to medium effect sizes [16–20]. Reviews focusing exclusively on the psychotherapy of depression in childhood and adolescence [16, 21] reported an overall effect size (g) of 0.36 at post-treatment and 0.21 at follow-up. A meta-analysis that focused on changes in child and adolescent depression-treatment effects over time revealed that mean effects drop significantly between post- and follow-up assessments [22].

This study thus aims to improve the treatment of depression in children and adolescents by focusing on how depression develops in children and adolescents as well as important causative and maintaining factors. As there is evidence of an association between the relationship quality of caregivers and their children in internalizing symptoms [23, 24], we assume that the interaction of children, adolescents and their caregivers is related to the development of depressive symptoms. Specifically, dysfunctional caregiver-child interaction behaviors appear to promote the development of depressive disorders in children and adolescents [25–29]. This association is, of course, also influenced by the attachment style. Especially anxious and avoidant attachment are relevant in this case, as those have been shown to be related to depressive symptoms [30, 31]. Accordingly, changes in interactional behavior or attachment of the parents should be drivers of change in child and adolescent depression symptomatology [32–34].

The Cognitive Behavioral Analysis System of Psychotherapy (CBASP) is a disorder-specific and integrative treatment approach that entails psychodynamic and cognitive-behavioral elements as well as theories from the interpersonal school [35]. CBASP was originally developed for adult patients who have developed chronic depression due to childhood maltreatment and negative relationship experiences, and as most of them have already undergone many different treatment attempts without success, they can be described as therapy-resistant [36]. CBASP addresses formative relationship experiences by first identifying significant others and the accompanying basic assumptions and thought patterns (causal conclusions, imprints). Actual relationship expectations or fears (transference hypotheses) are then documented to be processed and, at best, corrected through interpersonal and behavioral interventions [37, 38]. In this way, patients benefit from new positive relational experiences that enable a changed perception of the self and of others. Meanwhile, various studies on CBASP have been conducted in different settings and variations, and CBASP is considered an evidence-based psychotherapy for adults with depressive disorders [39–42]. However, positive studies have nevertheless revealed a high relapse and dropout rate, especially among young adults with depressive disorders [43]. As there are currently no studies on CBASP for the treatment of children and adolescents with depression, we report here on a pilot study for which we first adapted CBASP to target these age groups. Based on research findings on the involvement of caregivers in psychotherapy [44–46], and positively evaluated modular interventions [47, 48], we designed a modular, individualized treatment program for children and adolescents called CBASP@YoungAge. This study aims to implement CBASP@YoungAge in clinical practice and to investigate its feasibility and effectiveness compared to an active treatment as usual control group in a non-randomized design.

### Objective

The objective of this study is to assess the feasibility and potential effectiveness of the CBASP@YoungAge outpatient treatment program designed to treat children and adolescents with depression and interpersonal problems. The study aimed (1) to examine the acceptability and feasibility of the modular treatment program for therapists, patients, and caregivers. We assess whether the therapist employs the modular approach and if the patients and caregivers understand the material and treatment structure and participate in the treatment. Furthermore, the study aims to (2) investigate potential changes in the patients’ depressive symptoms and in the interpersonal behavior between patient and participating caregivers during the treatment process and compared to post-treatment. We expect (3) that this treatment will lead to a greater alleviation of depressive symptomatology, to improved interpersonal behavior of children and caregivers, and to stronger long-term alleviation of the patients' symptomatology than treatment-as-usual (TAU) group. In addition, we expect (4) to observe a significantly higher proportion of parent involvement in the intervention group than in the control group.

## Methods/Design

This pilot study is a non-randomized, quasi-experimental pilot feasibility trial comparing CBASP@YoungAge with a TAU control group (the actual gold standard in psychotherapy research [49]), to evaluate the feasibility and effectiveness of CBASP@YoungAge with respect to the depressive symptoms of children and adolescents and their interpersonal behavior with caregivers. This protocol is reported according to the SPIRIT 2013 [50] statement (see Additional file 1: completed SPIRIT checklist). For a brief overview, see the WHO Checklist (Additional file 2: WHO Trial Registration Data Set).

### Study setting

As CBASP@YoungAge is an outpatient treatment program, the intervention group is implemented at the Child and Adolescents Psychotherapy Outpatient Clinic Marburg (KJ-PAM, Philipps-University Marburg) while the TAU control groups are implemented at the Center for Child and Adolescent Psychotherapy (Outpatient Clinic, Ruhr-University Bochum) and the Landau Psychotherapy Outpatient Clinic for Children and Adolescents. All outpatient clinics are based in Germany and leading psychotherapy institutions invoice the German health insurance companies. The therapists are psychotherapy trainees.

### Participants and sample size

Eligible participants are aged between 10 and 21 years and meet the criteria for depressive disorders, based on DSM-5 [51]. Inclusion is based on a structural clinical interview (Kinder-DIPS, parent or child version [52]). A participating caregiver is mandatory in the CBASP@YoungAge group, whereas caregiver participation in the TAU groups is not requested beyond the legal requirements. As psychotherapy is conducted in German, children and participating parents need to be sufficiently fluent in German. Further, sufficient cognitive level of participating children/adolescents is required for the patients to be able to follow the cognitive interventions. Since intelligence tests are part of the standard diagnostics in the participating outpatient clinics, this criterion is operationalized by an IQ of ≥ 80.

We exclude children or adolescents in case of ongoing psychotherapy, acute suicidality, or a disorder expression requiring a different and non-depression focused treatment (e.g., traumatic disorder, schizophrenia, or bipolar disorders) or an inpatient stay. We do not exclude comorbid disorders or ongoing psychopharmacotherapy to enhance the external validity and generalizability of our findings. In case of outpatient housing, youth in the CBASP@YoungAge treatment group can nominate a different adult to participate in the sessions, as long as there is at least one significant person able and willing to join treatment sessions. If more than one person wants to participate, that is also possible.

Sample size calculations are guided by the considerations of Hertzog [53]. Thus, the planning of a larger study by this investigation was important, as well as the capacities of the centers involved and the sample size and drop out rate of other comparable studies [54, 55]. We aim to recruit 44 participants (22 per treatment arm). Assuming a 60% retention rate during the trial [56], this will lead 38 treatment completers with complete data.

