### Trial interventions

#### CBASP@YoungAge intervention

Based on CBASP [35], we designed the modular, individualized treatment program CBASP@YoungAge for children and adolescents that targets depressive symptoms while additionally addressing interactional difficulties with primary caregivers [58]. The treatment program is manualized and generally applicable in other outpatient psychotherapy contexts. CBASP@YoungAge differs from the traditional CBASP approach in several aspects. First, the active involvement of significant primary caregivers in therapy is mandatory. Second, in line with different previous studies, we modified CBASP more than originally intended [47, 59–62]. Third, the treatment approaches are age-adapted. For detailed information about the CBASP@YoungAge intervention, see the treatment manual ([name], [name], [name]: CBASP@YoungAge – Ein Therapiemanual für das ambulante Setting, in preparation). A brief overview is given in Fig. 4 and in the text below.

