**Fig. 4 Fig4:**
[figure not shown]
Procedure and structure of the treatment program (CBASP@YoungAge)

CBASP@YoungAge is conceived for three different age groups (10–12, 13–16, 17–21 years) with depressive disorders and resulting interpersonal problems. It consists of nine different modules that combine aspects of cognitive behavioral therapy (CBT) and psychodynamic psychotherapy. Overall, the intervention consists of three treatment modalities. The first is the individual treatment format, where the therapists work with the child or adolescent on their specific issues. Additional individual sessions with the caregivers are also possible. Second, in the joint format the patient and related caregiver share one session where both work individually on the same topic with the therapist. Third, the joint format the patient and the caregiver participate in the therapy session together. In general, the choice of the appropriate format is left to the therapist, as individual structural conditions must also be considered. The treatment manual only makes recommendations.

This structure aims to provide the most individualized and personalized course of treatment possible while supporting the therapist in every variation. To personalize the treatment, therapists have various age-appropriate adaptation options in the material, as well as flexibility in handling the sequence and the modules’ duration.

The therapeutic relationship in CBASP and thus also CBASP@YoungAge is called “Disciplined Personal Involvement” (DPI) [38] and is characterized by an appreciative, open, and authentic basic attitude towards the patient. DPI is a special form of relationship building that includes the therapist’s personal inner world, thinking, emotions, and reactions to the patient’s behavior [58].

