The cultivating phase of CBASP@YoungAge is based on a modular course and can be personalized by the therapists in the modules’ order and implementation. It focuses on the Kiesler-Circle-Family-Training and situation analysis, as well as on additional symptoms requiring treatment in additional sessions. The Kiesler-Circle-Family-Training aims to change learned interpersonal behaviors. Past experiences are actively targeted with the patient and relevant others. The most important aim of the Kiesler-Circle-Family-Training setup is the enhancement of flexibility in interpersonal behavior with different family members/significant others. Participants are encouraged to distinguish between different positions in the Kiesler-Circle and are further trained in the perception and reflection of their behavior, evaluation of behavior effects and behavior adaptations to successfully master difficult interactions. During this module, caregivers participate in every session. Situation analysis is applied to enhance the patient’s self-efficacy and ability to act in difficult situations with other people. Patients are trained to notice that they can be in charge and actually change difficult situations. They learn how to shape situations differently to achieve new, changed outcomes for themselves.

The consolidation phase focuses on relapse prevention, reviews the therapy, and checks whether previously set goals have been achieved.

CBASP@YoungAge covers 20 to 30 sessions. Frequency is at least once a week and up to three times a week. It is up to the therapist to decide which modules to use and when based on the individual patient and her/his caregivers. After treatment completion, booster sessions can take place.

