#### Treatment-as-usual control group

The TAU control group is implemented in two cooperating outpatient clinics. The responsible therapists are also psychotherapists in training who are under regular case supervision.

Treatment is based on psychotherapy guidelines [63] and current evidence-based practices for the treatment of depression in childhood and adolescence. No further restrictions with respect to duration or length are made. Family involvement is based on the current psychotherapy accounting rules of the German health care system (every 4th session).

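### An adult willing to join sessions is an entry condition for CBASP@YoungAge but not for TAU, an avoidable and unlisted selection difference; aim 4 then largely restates the design

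*Protocol article*

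**What the plan says.** The caregiver rule stands among the eligibility criteria in Participants and sample size: "A participating caregiver is mandatory in the CBASP@YoungAge group, whereas caregiver participation in the TAU groups is not requested beyond the legal requirements." For young people in out-of-home care, the same section lets those in the CBASP@YoungAge group name another adult, "as long as there is at least one significant person able and willing to join treatment sessions." No such provision is written for TAU.

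The section CBASP@YoungAge intervention repeats the requirement as a feature of the treatment: "First, the active involvement of significant primary caregivers in therapy is mandatory." Of the Kiesler-Circle-Family-Training it says: "During this module, caregivers participate in every session." For the programme in general, however, "the choice of the appropriate format is left to the therapist." Under Treatment-as-usual control group the article says: "Family involvement is based on the current psychotherapy accounting rules of the German health care system (every 4th session)."

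Two aims in the Objective depend on these rules. Aim 3 compares the arms and expects "that this treatment will lead to a greater alleviation of depressive symptomatology" than under TAU. Aim 4 reads: "we expect (4) to observe a significantly higher proportion of parent involvement in the intervention group than in the control group." The Statistical analysis section plans intention-to-treat analyses, with ANCOVA for the difference between the groups after the intervention and at follow-up. The limitations in the Discussion name the quasi-experimental design with site effects, the staggered start, uncaptured aspects such as the therapeutic alliance, the absence of numeric progression criteria, and the lack of blinding. They do not name the different entry rule.

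**The concern.** There are two linked problems.

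First, the arms do not draw on the same kind of family. A patient without an adult prepared to attend is barred from one arm and admitted to the other. The Background holds that dysfunctional caregiver-child interaction seems to promote depression, and that change in parental interaction or attachment should drive symptom change. On that reasoning, having an adult willing to take part may bear on how a patient does under any treatment. A between-arm difference under aim 3 could then partly reflect who was allowed in. The clinic effect is built into the layout of the study. This difference is not, because it can be screened for or recorded.

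Second, aim 4 predicts as a finding something that the protocol largely prescribes: caregiver involvement is compulsory in one arm and follows an accounting rule of one session in four in the other.

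Both matter because the study is meant to show the potential of including caregivers and to inform the power calculation for a later randomised trial.

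**Working it through.** The plan gives no figure for this point, so there is none to reproduce. The check compares the stated rules and then illustrates their possible effect. All values of q and g below are assumptions.

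**1. Is the rule an entry condition?** Yes. It stands with the inclusion criteria, and the provision for out-of-home care makes a willing adult a condition in the CBASP@YoungAge arm. For TAU no such willingness is asked.

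**2. How far is TAU already filtered?** Recruitment and procedure takes written consent from the primary caregiver and the patient without distinguishing arms, and TAU families are involved about one session in four. TAU families are therefore not unselected. What remains is the gap between consenting to a study and being prepared to join treatment sessions.

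**3. Possible bias in the arm comparison.** Let q be the share of TAU patients without a willing adult, and g their deficit in outcome (in SD) relative to patients who have one. With no treatment effect, the CBASP@YoungAge mean is m and the TAU mean is (1 − q)m + q(m − g) = m − qg. The spurious difference is q × g. With the planned 22 per arm and an unadjusted comparison, SE = √(2/22) = 0.302 SD. The two-sided 5% test rejects with probability 1 − Φ(1.96 − qg/SE) + Φ(−1.96 − qg/SE). Each cell gives the bias in SD and, in brackets, the rejection rate:

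| q | g = 0.3 | g = 0.5 | g = 0.8 |
|---|---|---|---|
| 0.1 | 0.03 (5.1%) | 0.05 (5.3%) | 0.08 (5.8%) |
| 0.2 | 0.06 (5.5%) | 0.10 (6.3%) | 0.16 (8.3%) |
| 0.3 | 0.09 (6.0%) | 0.15 (7.9%) | 0.24 (12.5%) |
| 0.5 | 0.15 (7.9%) | 0.25 (13.2%) | 0.40 (26.4%) |

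At q = 0 the bias is zero and the test keeps its 5%. If g is negative, the bias favours TAU.

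**4. Aim 4, read as the share of patients with any caregiver participation.** Under the entry rule CBASP@YoungAge is 22/22, so TAU cannot exceed it and the result depends on TAU alone. With 22/22 against x/22, Fisher's two-sided p is 2 × C(22, 22−x)/C(44, 22−x):
- x = 18: 2 × 7,315/135,751 = 0.108.
- x = 17: 2 × 26,334/1,086,008 = 0.048.

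The test is significant once five or more TAU patients have no caregiver participation, and not otherwise.

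**5. Aim 4, read as the share of sessions.** The TAU rule implies about 25%, which is 5 to 7.5 sessions if a TAU course ran to the 20 to 30 sessions given for CBASP@YoungAge. In CBASP@YoungAge, the Kiesler-Circle module alone passes 25% if it takes more than 5 of 20 or more than 7.5 of 30 sessions, even with no caregiver elsewhere. The article does not give the module's length and leaves format to the therapist. A higher share is thus what the protocol points to, but no minimum total is fixed.

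**The case against.** The strongest reply is that the harm is not shown. The Background passage concerns the quality of caregiver-child interaction, not readiness to attend sessions. The programme addresses depression with interpersonal problems, so the CBASP@YoungAge clinic might attract more conflicted families, and the bias could run against it. Consent and family sessions in TAU may leave very few patients without a willing adult. This stands: neither the size nor the sign can be read from the article, and the table shows little distortion where q and g are small.

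A reader might go further in several ways that the article does not support:
- **That a known part of any CBASP@YoungAge advantage is spurious.** This needs values of q and g that the article does not contain. Setting the bias against the effect of 0.36 in the Background does not help: that is an overall psychotherapy effect with no comparator stated, not an expected difference from active TAU.
- **That caregiver-completed questionnaires will be selectively missing in TAU.** Outcomes has caregivers complete assessments without distinction by arm, and not attending sessions is not the same as not returning a form.
- **That aim 4 is true by construction and uninformative.** Session format is flexible, significance is not assured, and in a feasibility study it is useful to know whether the prescribed involvement took place.
- **That ANCOVA wrongly omits a caregiver covariate.** Covariates are commonly left to the analysis plan, which is not at hand.
- **That the bias can be removed at no cost.** Patients may be lost from the comparison, and arm stays fully confounded with clinic.

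None of this removes the asymmetry. It is written into the eligibility criteria, bears on a comparison the protocol intends to make, and is missing from the stated limitations.

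**Conclusion.** The point holds in a limited form. The two arms have different caregiver entry rules on a factor that the protocol's own rationale makes plausibly prognostic. This is an avoidable selection difference on top of the acknowledged site confounding, and it should be disclosed and reduced. Its magnitude is unknown. The 0.03 to 0.40 SD in the table rests wholly on assumed values of q from 0.1 to 0.5 and g from 0.3 to 0.8 SD, and values near zero or of the opposite sign are compatible with the article.

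Aim 4 largely, though not strictly, restates the design. A significant difference would show that the protocol was delivered and that the arms were separated in caregiver involvement. It would not show an effect of the treatment.

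**What to change.** - **Patients still to be enrolled.** At screening in all three clinics, before treatment, ask whether at least one significant adult is able and willing to take part in sessions. Apply the same requirement to the between-arm comparison and leave TAU delivery as it is. Trial status expects control recruitment to run until December 2022; if it has closed, only the remaining items apply.
- **TAU patients already enrolled.** Record the answer, keep the planned intention-to-treat comparison, and add a comparison restricted to, or adjusted for, caregiver availability. State that an answer given after treatment began may be affected by that treatment. For this reason it should not define the main analysis.
- **Aim 4.** Report it as a delivery measure: sessions with a caregiver divided by all sessions, by arm, with a confidence interval that allows for repeated sessions within patients. Drop the claim of significance.
- **Limitations.** Name the different entry rule beside the site effects.

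The cost is one screening question, a flag for enrolled TAU patients, and a somewhat smaller TAU group in the restricted comparison. Under the assumed q of 0.1 to 0.5, 22 × q is about 2 to 11 TAU patients. A stated willingness in TAU is not identical to accepting actual participation in CBASP@YoungAge, and the confounding of arm with clinic remains.

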### Statistical analysis

A preliminary analysis of the results after post-assessment is planned. A full analysis will follow the completion of all follow-up assessments. Data will be analyzed based on the Intention-to-treat (ITT) sample and will help inform power calculations for a future CBASP@YoungAge randomized control trial.

Central aspects with regard to feasibility in the analysis are attrition and reasons for drop-out of patients or parents. These aspects will be recorded and analyzed. Recruitment rate is measured by reporting the number and reasons of patients screened for the intervention group who decided against study participation. We also capture the proportion of patients who participate in each arm at pre-, post- and 6-month follow-up assessment. Furthermore, we access the proportion of patients meeting criteria for response and remission based on the Kinder-DIPS at the different time points. With regard to attrition, therapists will assess the number of sessions of the modules, and the session frequency in general and related to the different modules. In addition, we will record each participant’s individual course of therapy in self-reports, and reports from others, as well as any unexpected events in the course of therapy. For participants who withdraw from the study, the researcher will follow-up with either the therapists or participants to document their reason(s) for study withdrawal. We will assess rates and types of missing data, and the proportion of drop-outs at different stages throughout the trial. We will also assess whether any of the measures display floor and/or ceiling effects. Patient adherence to treatment will be indexed by the mean (SD) number of therapy sessions offered and attended, and by calculating the proportion of participants who undergo a minimum adequate dose (eight or more sessions) in each arm. Adherence of protocol by therapists is analyzed descriptively by the proportion of complete adherence checks and the monitoring of individual case and data management in the study routine. Data completeness is reported as proportions of missing values. Due to sample size and this study’s pilot character, the feasibility analysis is mainly based on the intervention group’s process evaluation. First-interim analyses of results are only possible with sufficient post-measurements. Missing values will be integrated in an iterative imputation method based on a random forest model.

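### The recruitment target (44), the retention rate (60%) and the completer count (38) cannot all be true, and the protocol does not show which is wrong

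*Protocol article*

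**What the plan says.** The sample-size rationale is one short paragraph in the protocol article, under Participants and sample size. It attributes the size to published pilot-study considerations, the needs of planning a larger study, the capacity of the centres, and the size and dropout of comparable studies. It states no significance level, power, effect size or standard deviation. Its numbers are in two consecutive sentences. The first sets the target, "We aim to recruit 44 participants (22 per treatment arm", and the second gives the expected yield: "Assuming a 60% retention rate during the trial [56], this will lead 38 treatment completers with complete data".

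Two statements under Statistical analysis bear on what the yield means. On the analysis set: "Data will be analyzed based on the Intention-to-treat (ITT) sample and will help inform power calculations" for a later randomised trial. On incomplete data: "Missing values will be integrated in an iterative imputation method based on a random forest model".

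**The concern.** The second sentence presents 38 as the consequence of applying 60% retention to the 44 recruits of the first. It is not, and the gap is too large to be rounding.

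Three things hang on it.

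- The expected number of completers is the only quantitative result in the paragraph, since no power calculation is given.
- Patient dropout is named under Outcomes as part of the primary feasibility outcome, and Statistical analysis treats attrition as central. Yet the paragraph implies both 40% and about 14% dropout. An observed dropout of 25%, say, would be better than expected on one figure and worse on the other.
- Imputing for roughly 14% of 44 non-randomised participants is a different undertaking from imputing for roughly 40%. The results are also meant to inform the power calculation of the next trial.

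**Working it through.** **Inputs**, all from Participants and sample size: recruits N = 44 (22 per arm); retention r = 0.60; stated completers with full data S = 38.

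**1. Attempt to reproduce the stated figure.** Completers = N × r = 44 × 0.60 = 26.4, about 26. Per arm: 22 × 0.60 = 13.2, about 13. The stated 38 is not reproduced; the gap is 38 − 26.4 = 11.6, about 12.

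**2. Other readings of the 60%.** None comes within two patients of 38.

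| Reading | Arithmetic | Completers |
|---|---|---|
| Rounded up within each arm | 2 × 14 | 28 |
| 60% is dropout, not retention | 44 × 0.40 | 17.6 |
| Attrition in one arm only | 22 + 22 × 0.60 | 35.2 |
| Division by 1 + dropout | 44 / 1.4 | 31.4 |
| Division by 1 + retention | 44 / 1.6 | 27.5 |
| 44 per arm instead of in total | 88 × 0.60 | 52.8 |
| 60% applied twice | 44 × 0.60 × 0.60 | 15.8 |

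Separating retention in the trial from completeness of data does not help. A participant with full data has to have been retained for the assessments, so that distinction can only lower the count.

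**3. Reverse check.**
- Retention implied by 38 of 44: 38 / 44 = 0.864, so dropout is 13.6% (6 of 44).
- Recruits needed for 38 completers at 60%: 38 / 0.60 = 63.3, so 64.
- Recruits from the common slip of multiplying by 1 + dropout: 38 × 1.4 = 53.2, so 54. That is not 44 either.

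**4. Could 38 be a lucky outcome at 60%?** For a binomial count with 44 trials and probability 0.60, P(38 or more) ≈ 0.0001.

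**5. Consequences if 60% is right.**
- Completers: 26 instead of 38, a shortfall of 12 / 38 = 32%.
- Without full data: 1 − 0.60 = 40%, against 1 − 0.864 = 13.6%.
- Illustrative precision: the half-width of a 95% confidence interval for an unadjusted, complete-case difference between arms, in SD units, is 1.96 × √(2/n) with n completers per arm.
  - n = 13: 1.96 × √(2/13) = 0.77
  - n = 19: 1.96 × √(2/19) = 0.64
  - n = 22 (no dropout), for reference: 1.96 × √(2/22) = 0.59

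The half-widths assume equal dropout in the two arms and a normal quantile. With t quantiles the first two become about 0.81 and 0.66.

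**The case against.** The arithmetic is hard to dispute; the inferences drawn from it can be. A reader might go further in several ways that the document does not support.

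- **That 38 is the error.** The paragraph does not show this. The slip may be in the 60%, and if the cited source supports about 86% then no yield is overstated. The retention source cannot be consulted here. This objection stands in full.
- **That the analysable sample shrinks by 12.** Under Statistical analysis the analysis set is intention-to-treat with imputation, so it is nominally 44 either way. What changes is how many of the 44 rest on imputed values.
- **That the precision of every feasibility proportion changes.** Recruitment is counted among those screened. Dropout, participation at each assessment and receipt of a minimum number of sessions naturally use enrolled participants. Feasibility is also to rest mainly on session-by-session process evaluation in the intervention group. The completer count matters chiefly for post-treatment and follow-up estimates among completers, and for the SD taken from them.
- **That 40% of post-treatment data would be missing.** The sentence speaks of retention over the trial, and assessments continue to six months. It does not tie the rate to the post-treatment visit.
- **That the half-widths are the trial's own precision.** The plan is ANCOVA, and covariate adjustment would typically narrow them. They only show the scale of the difference.
- **That the retention figure should become a feasibility threshold.** The Discussion explains that numeric progression criteria could not be set because of the pandemic. Asking for one here would be a preference, not a correction.

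It is also fair to say that nothing presents 44 as derived from 38, so the recruitment target does not fall with the yield. None of this reconciles the three numbers.

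**Conclusion.** The inconsistency is certain: 44, 60% and 38 cannot hold together, and no other part of the article resolves them. The discrepancy is about 12 completers (26 against 38) or, put the other way, about 26 percentage points of retention (60% against 86%). Which figure is at fault cannot be settled from the document.

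The consequences in step 5 are conditional on 60% being right, and the interval widths are illustrative. A reader might infer that the trial is underpowered; the document gives no basis for that, because it makes no power claim. The point still needs correcting, because it is a stated sample-size figure that is wrong as written, in the only sample-size rationale shown.

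**What to change.** Check the retention rate in the source the protocol cites, keep the target of 44, and make the sentence agree with itself in one of two ways:

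- if 60% is what the source supports, restate the yield as about 26 participants with full data, about 13 per arm;
- if 38 is the intended yield, correct the retention rate to about 86% (about 14% dropout).

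Either costs one sentence and no additional patients; the first also means printing a less favourable number. Holding on to both 60% and 38 would instead require 64 recruits. That is a different study size from the one the paragraph ties partly to centre capacity, so it is not an editorial correction.
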